### Outcomes {12}

The primary outcome is postoperative complications measured by the Comprehensive Complication Index (CCI) at 90 days after surgery [20, 21]. The CCI expresses postoperative morbidity on a continuous numeric scale from 0 (no complication) to 100 (death) by weighing all postoperative complications according to the validated Clavien-Dindo classification [22] for their respective severity [23]. It is measured at the end-of hospitalization and 90 days after surgery to include cases in which readmission was necessary. Postoperative complications are the gold standard in the evaluation of the quality of surgery as they directly reflect the procedures outcome and are most relevant for the patients.

Secondary endpoints are postoperative morbidity along the classification of Clavien-Dindo at the end of hospitalization as well as 90 days +/− 2 weeks after surgery [22, 23]. We will further analyse major complications ≥3b after 90 days. This classification consists of five (1–5) severity grades. Grade 1 reflects minor complications, while grade 5 reflects death. The classification is widely accepted and validated to report postoperative complications. It is also reported at the end of hospitalization as well as 90 days after surgery.

Further secondary endpoints are length of hospital stay (LOS), readmission rate (during 90 days) and mortality (during 90 days) as a reflection of postoperative outcome.

Physiotherapeutic values are the MIP, LOAD, POWER, and Breathing Energy. MIP is the most commonly used measure to evaluate inspiratory muscle strength. Very sensitive in detecting early respiratory muscle dysfunction, it allows for the assessment of ventilatory failure, restrictive lung disease and respiratory muscle strength and therefore represents a clinically meaningful trial endpoint [24]. Further secondary endpoints are Load(cmH20), Power (Watt), Energy (Joule), Volume(l), and sit-to-stand test.

(LOAD) is a measure of resistance to inhalation, and represents the pressure generated in the airways due to the force of the inspiratory muscles during a training session. As the training load decays with increasing lung volume (in order to match the length-tension characteristics of the inspiratory muscles), the load displayed corresponds to the resistance at the start of inhalation (i.e. at RV). A higher load result means that the patient is training their inspiratory muscles harder, leading to stronger muscles. Stronger inspiratory muscles will need to work less hard to cope with the demands of breathing, leading to reduced breathlessness [cmH20].

(POWER) is a measure of muscle performance which combines strength and speed of movement (pressure × flow). More powerful muscles will be more resistant to fatigue at a given level of work and therefore, breathlessness will be reduced. The value displayed is the average power for all breaths in a training session.

(Breathing Energy) is a measure of the mechanical work (or effort) of breathing during your breathing training session. It is a result which combines the force exerted by your inspiratory muscles and the volume (1) of air inhaled. The higher the value of breathing energy you attain, the longer and harder you have worked your inspiratory muscles.

During the sit-to-stand test, the quantity [n] how often a patient can sit down on a chair and stand up during 60 s is noted. These values are evaluated at admission to hospital for surgery and 5 days after surgery.

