### Intervention description {11a}

Once patients give their informed consent to the study and are assigned to the intervention group, physiotherapists will measure the maximal inspiration pressure (MIP) with the POWER®breathe device of each single patient. Patients will then be instructed to perform inspiratory muscle training at the level of 60% of their MIP. Patients are instructed to perform the training containing 30 breaths twice a day for 14–18 days before surgery. After 7 days of training, a physiotherapeutic control will be performed to check compliance and training performance and to answer open questions. The devices are able to register the performance of each single training session and training results are monitored.

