## Participant timeline {13}

The participant timeline is shown in Table 1.

**Table 1 Tab1:** Participant timeline

***Visit***	***1***	***2***	***3***	***4***		***6***	***7***	***8***
*Time (day)*		***0***	***7 +/-2d*** ^***a***^	***14 +/-4d***	*0*	***5+/-2d pod***	***x pod***	***90+/-14 pod***
*Patient schedule*	***Screening visit***	***Baseline visit***	***Compliance visit***^a^	***Admission to hospital***	***Surgery***	***Day 5 after surgery***	***End of hospitalisation***	***End of study visit***
*Hospital status*	*Outpatient*				*Inpatient*			*Outpatient clinic*
*Patient information and informed consent*	*x*							
*Demographics*	*x*							
*Medical history*	*x*			*x*				
*Medication*^b^	*x*			*x*			*x*	
*In-/exclusion criteria*	*x*	*x*						
*Administer medical device and training instruction*		*x*						
*Inspiratory muscle training (IMT)*		x	*x*	*x*				
*Power®Breathe device*		*KHP2*^*c*^*,KH2*	*KHP2*	*KHP2*^d^		*KH2*		
*Compliance check and training performance*			*x*					
*VAS/NRS/ Vital signs*				*x*		*x*	*x*	
*BMI*	*x*			*x*				
*Maximum inspiratory pressure*		*x*		*x*		*x*		
*Load (cmH20), Power (Watt), Breathing Energy (Joule), Volume (l)[measured by Power®Breathe device*]		*x*	*x*	*x*		*x*		
*Sit-to-stand test*		*x*		*x*		*x*		
*(Serious) Adverse events*		*x*	*x*	*x*		*x*	*x*	*x*
*Complications*							*x*	*x*

^a^When IMT (inspiratory muscle training) > 15 days, patients are offered an additional appointment with physio on demand, scheduled training can be extended up to 6 weeks

^b^Antibiotics, immunosuppressants, anticoagulants, insulin, oral antidiabetics

^c^Hand out Power®Breathe KHP2 device by a physiotherapist to patient

^d^Return of Power®Breathe KHP2 device to the physiotherapist on the ward

*pod* postoperative day, *VAS* visual analogue scale, *NRS* numerical rating scale, *BMI* body mass index

Control group starts at Visit4: hospital admission. The postoperative procedure is the same for both groups

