The length of stay (LOS) will be analysed as time to hospital discharge alive, using a Cox proportional hazards model. If there are patients who died during the hospital stay, in-hospital death will be considered as competing risk and patients will be censored at the date of death in a cause-specific Cox proportional hazards model. The binary outcomes readmission and mortality within 90 days will be compared with a logistic regression model. MIP, Load, Energy, Power, Volume and the sit-to-stand test results, which are measured multiple times per patient, will be compared with linear mixed-effects models with a random intercept per patient to account for the non-independence of repeated measurements on the same patient. Treatment will be used as explanatory factor with age, BMI, disease localization and disease dignity as covariates in the statistical models as in the analysis of the primary outcome. In addition, time of measurement and the interaction of time and treatment will be included in the mixed-effects models. Secondary outcomes will be evaluated using complete case analysis applied to the FAS.

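### Load and session-total Breathing Energy are defined largely as training dose, yet are compared between arms as outcomes, with a change of device model between the two visits both arms share

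*Protocol article*

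**What the plan says.** Outcomes {12} of the protocol article makes Load, Power, Energy and Volume secondary endpoints beside MIP and the sit-to-stand test, and evaluates them at admission and on day 5 after surgery. It describes them as follows.

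- **Load** "represents the pressure generated in the airways due to the force of the inspiratory muscles during a training session". Also: "the load displayed corresponds to the resistance at the start of inhalation", and "A higher load result means that the patient is training their inspiratory muscles harder, leading to stronger muscles".
- **Power**: "The value displayed is the average power for all breaths in a training session". The same paragraph presents it as an index of how the muscle performs, joining strength and speed.
- **Breathing Energy**: "The higher the value of breathing energy you attain, the longer and harder you have worked your inspiratory muscles".
- **Volume** is listed but not given a definition of its own.

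Intervention description {11a} says of the training arm: "Patients will then be instructed to perform inspiratory muscle training at the level of 60% of their MIP".

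Statistical methods {20a}: "MIP, Load, Energy, Power, Volume and the sit-to-stand test results, which are measured multiple times per patient, will be compared with linear mixed-effects models", with treatment, time and their interaction in the model.

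Table 1 in Participant timeline {13} gives KHP2 and KH2 at baseline, KHP2 at the compliance visit and at admission (Visit 4), and KH2 on day 5. The Visit 4 entry carries the footnote "Return of Power®Breathe KHP2 device to the physiotherapist on the ward". A note under the table says that controls start at Visit 4 and that postoperative procedures are common to both arms. Blinding {17a} defends the open-label design partly on the ground that the outcomes are recorded in the KHP2.

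**The concern.** A between-arm outcome should be obtained in the same way in both arms and should not be a restatement of the intervention. Load and session-total Energy, as described, rise when a patient trains against more resistance or for longer. One arm arrives at admission after at least two weeks of such sessions and the other after none.

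Two things are at stake. A difference in Load or Energy at admission could be reported as a physiotherapeutic benefit when part of it comes from the setting, the number of breaths, the device or familiarity with it. And the change from admission to day 5, which should describe the effect of surgery, also contains any difference in reading between the two models.

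**Working it through.** The article gives no target or expected value for these endpoints, so there is no figure of its own to reproduce here. Its sample size concerns only the CCI and is not in question: a two-sided t test with difference 6, SD 10, alpha 0.05 and power 0.90 gives 59.35, so 60 per arm and 120 in total, and 120 / 0.9 = 133.3, so 134.

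**Step 1: what both arms share.** Controls enter at Visit 4. Only admission and day 5 can be compared between arms.

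**Step 2: Load.** Write Load = f × MIP, where f is the fraction set. The 60% is documented for training; MIP values of 60, 80 and 100 cmH2O are assumed.

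| MIP (assumed) | f = 0.6 | f = 0.6, MIP up 10% | f = 0.5 or 0.7, MIP unchanged |
|---|---|---|---|
| 60 | 36 | 39.6 | 30 or 42 (∓6) |
| 80 | 48 | 52.8 | 40 or 56 (∓8) |
| 100 | 60 | 66.0 | 50 or 70 (∓10) |

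If f is fixed at 0.6 of same-visit MIP, Load carries a strength gain but only repeats MIP. If f varies, Load moves with no gain at all. The article does not say which applies at the two shared visits.

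**Step 3: Energy and Power.** Session energy = n × e, with n breaths and energy e per breath. The prescribed session has 30 breaths; a control stopping at 15 is an assumption. The ratio is 30e / 15e = 2 at equal load and volume. Since e goes roughly with pressure × volume, a load progressed by 20% (assumed) raises e by about 20% at the same volume. Power is averaged over breaths, so n drops out, but as pressure × flow it still depends on the load.

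**Step 4: device.** Let d be an additive KHP2 minus KH2 offset; its value is not given and may be zero.

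| Comparison | Effect of d if controls use KHP2 at Visit 4 | Effect of d if controls use KH2 at Visit 4 |
|---|---|---|
| Between arms, admission | cancels | shifted by d |
| Between arms, day 5 (KH2 in both) | none | none |
| Admission to day 5, training arm | shifted by −d | shifted by −d |
| Admission to day 5, controls | shifted by −d | none |
| Time × treatment | cancels | shifted by −d |

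The only KHP2 entry at Visit 4 is tied to handing back a personal unit, which controls never had. Which column applies is therefore not settled by the table. Blinding {17a} names only the KHP2, although the day 5 entry is KH2.

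**The case against.** The strongest reply has four parts.

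1. **The text also speaks of function.** It relates Load to the force of the inspiratory muscles and presents Power as muscle performance. A reader might infer that the comparison shows only that the training arm trained, and nothing about function. The documents do not support that: a like-for-like test in both arms could show a real gain, above all in Power. Nor do they say that Load at the assessments is the prescribed resistance. The 60% is an instruction for training, and a Load tied to same-visit MIP would be redundant rather than circular.
2. **Not every value is a session total.** Volume is never defined as a session read-out, and Power and Load do not scale with the number of breaths. Counting four of the six physiotherapy measures as equally compromised would go too far.
3. **The device switch is common to both arms on day 5.** It then acts on time, not on arm, and a common shift is absorbed by the time term. No difference in reading between the models is documented. The KHP2 entries at baseline and Visit 4 may partly record hand-out and return.
4. **Assessment details belong in the full protocol, and these are secondary endpoints.** The Discussion itself says that physiotherapy values do no more than correlate with surgical outcome.

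Parts 1 to 3 stand and limit the point. Part 4 stands as to importance and unreported detail. It does not answer what the article does state: definitions that tie Load and Energy to training effort, their use as between-arm outcomes, and a device row at odds with the blinding section.

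**Conclusion.** The point holds in a limited form. By the article's own definitions, Load and session-total Energy largely index how hard and how long a patient trained, and Power is a session average. Their comparison at admission can be partly an artefact of setting, breath count, device or familiarity, and the admission-to-day-5 change is mixed with a change of model.

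The size cannot be derived. The factor of 2 for Energy and the 6 to 10 cmH2O for Load rest on assumed breath counts, MIP values and settings; the device offset is unknown. The day 5 comparison between arms is free of the device problem. MIP is touched only through the Visit 4 device. The CCI analysis and the sit-to-stand test are not affected. The matter deserves correction because values already collected under unlike conditions cannot be made comparable by analysis.

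**What to change.** - Name MIP and sit-to-stand as the functional physiotherapy endpoints.
- Report Load as a setting or as intervention delivered, not as an outcome.
- If Power, Energy and Volume stay as between-arm outcomes, take them at admission and on day 5 in both arms from one identical assessment: same device model, same number of breaths, same percentage of same-visit MIP. Express Energy per breath. The KH2 is already scheduled for day 5, so choosing it would change only the Visit 4 entry; the same model should then serve for MIP.
- Reconcile Blinding {17a} with the device row of Table 1, and separate the hand-out and return of training units from the measuring device.

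Restricting all four values to the training arm is not advised, because it would discard the randomised day 5 comparison.

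The cost is one fewer secondary endpoint, a short standard test at Visit 4, and an amendment, since the article's section on protocol amendments {25} requires ethics committee approval for changes to endpoints. The first patient was enrolled in August 2021, so patients measured before the change should be flagged in the data and in the report.

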## Participant timeline {13}

The participant timeline is shown in Table 1.

**Table 1 Tab1:** Participant timeline

***Visit***	***1***	***2***	***3***	***4***		***6***	***7***	***8***
*Time (day)*		***0***	***7 +/-2d*** ^***a***^	***14 +/-4d***	*0*	***5+/-2d pod***	***x pod***	***90+/-14 pod***
*Patient schedule*	***Screening visit***	***Baseline visit***	***Compliance visit***^a^	***Admission to hospital***	***Surgery***	***Day 5 after surgery***	***End of hospitalisation***	***End of study visit***
*Hospital status*	*Outpatient*				*Inpatient*			*Outpatient clinic*
*Patient information and informed consent*	*x*							
*Demographics*	*x*							
*Medical history*	*x*			*x*				
*Medication*^b^	*x*			*x*			*x*	
*In-/exclusion criteria*	*x*	*x*						
*Administer medical device and training instruction*		*x*						
*Inspiratory muscle training (IMT)*		x	*x*	*x*				
*Power®Breathe device*		*KHP2*^*c*^*,KH2*	*KHP2*	*KHP2*^d^		*KH2*		
*Compliance check and training performance*			*x*					
*VAS/NRS/ Vital signs*				*x*		*x*	*x*	
*BMI*	*x*			*x*				
*Maximum inspiratory pressure*		*x*		*x*		*x*		
*Load (cmH20), Power (Watt), Breathing Energy (Joule), Volume (l)[measured by Power®Breathe device*]		*x*	*x*	*x*		*x*		
*Sit-to-stand test*		*x*		*x*		*x*		
*(Serious) Adverse events*		*x*	*x*	*x*		*x*	*x*	*x*
*Complications*							*x*	*x*

^a^When IMT (inspiratory muscle training) > 15 days, patients are offered an additional appointment with physio on demand, scheduled training can be extended up to 6 weeks

^b^Antibiotics, immunosuppressants, anticoagulants, insulin, oral antidiabetics

^c^Hand out Power®Breathe KHP2 device by a physiotherapist to patient

^d^Return of Power®Breathe KHP2 device to the physiotherapist on the ward

*pod* postoperative day, *VAS* visual analogue scale, *NRS* numerical rating scale, *BMI* body mass index

Control group starts at Visit4: hospital admission. The postoperative procedure is the same for both groups

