### Strategies to improve adherence to interventions {11c}

The POWER®breathe KHP2 devices are able to register the performance of each single training session so that all training results are stored. Furthermore, we are calling the patient on a regular basis, to improve adherence or to detect potential problems. Patients will not have to keep up-to-date records of their training.

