### Implementation {16c}

The randomization is performed in a 1:1 ratio to either the intervention or the control arm of the study with SecuTrial® at the CTC at the University of Zürich.

Enrolling of patients will be performed by DB, KP or AM.

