### Adverse event reporting and harms {22}

The investigator has the responsibility for SAE identification, documentation, and assessing the causal relationship study intervention.

All SAEs will be fully documented in the appropriate *eCRF*. For each SAE, the investigator will provide the onset, duration, treatment required, outcome and action taken with regard to the study intervention.

If, during a clinical trial, serious adverse events occur in participants in Switzerland, and it cannot be excluded that the events are attributable to the intervention under investigation, the investigator must report these events:
To the CEC within 15 days.

If immediate safety and protective measures (with possible relation to the POWER®Breathe device) have to be taken during the conduct of this clinical trial, the investigator must notify the CEC of these measures, and of the circumstances necessitating them, within 7 days.

Participants terminating the study (either regularly or prematurely) with the following will return for a follow-up investigation:
Reported ongoing SAE, orAny ongoing AEs of laboratory values or of vital signs being beyond the alert limit

This visit will take place up to 30 days after terminating the treatment period. Follow-up information on the outcome will be recorded on the respective SAE page in the eCRF.

Follow-up investigations may also be necessary according to the investigator’s medical judgement even if the participant has no SAE at the end of the study. However, information related to these investigations does not have to be documented in the eCRF but must be noted in the source documents.

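### Before admission, adverse events are actively sought only in the training arm, so an adverse event summary by arm that includes this period is not like for like

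*Protocol article*

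**What the plan says.** In Participant timeline {13}, Table 1 marks (serious) adverse events at Visit 2 (baseline, day 0), Visit 3 (compliance, day 7), Visit 4 (admission), and Visits 6, 7 and 8. The note under the table reads "Control group starts at Visit4: hospital admission" and continues "The postoperative procedure is the same for both groups". Another footnote to the table says that "scheduled training can be extended up to 6 weeks".

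Strategies to improve adherence to interventions {11c} adds a further contact: "we are calling the patient on a regular basis, to improve adherence or to detect potential problems".

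Adverse event reporting and harms {22} makes the investigator responsible for identifying SAEs and says "All SAEs will be fully documented in the appropriate" eCRF. It sets no limit by arm or by period.

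Under Outcomes {12}, "The primary outcome is postoperative complications measured by the Comprehensive Complication Index (CCI) at 90 days after surgery". Complications are recorded at Visits 7 and 8.

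**The concern.** Eligibility criteria {10} require surgery to be planned at least two weeks after inclusion, and patients are randomised once they have consented. Both arms therefore spend weeks in the trial, as randomised patients, before they are admitted. Infections, unplanned admissions or worsening disease can occur in either arm during that time. The schedule looks for such events in one arm only, and the trial is open label.

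Two things are at stake. First, a count of adverse events by arm over the whole study would favour controls even if training were harmless. Second, the investigator must judge whether SAEs are related to the intervention, and in the weeks of preoperative training there is no comparable record of background events in controls. A control whose operation is cancelled may never reach Visit 4, so a question asked only at admission would not reach that patient.

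**Working it through.** **Does the asymmetry follow from the text?** Set side by side:

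| Period | Training arm | Control arm |
|---|---|---|
| Randomisation to admission | Visits 2 and 3, both with adverse event recording; regular calls | No scheduled visit |
| Admission | Visit 4, adverse event recording | Visit 4, adverse event recording |
| After surgery | Visits 6, 7 and 8 | Visits 6, 7 and 8 |

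Intervention description {11a} supports this reading: the first device measurement and the training instruction follow consent and assignment to the intervention group. That the calls go to trainees only is an inference from the section in which they are listed, since controls have no preoperative training to adhere to.

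**The plan's own figures.** The document gives no adverse event rate and no observation-time figure to reproduce. Its sample size does reproduce: a two-sample t test with a difference of 6, SD 10, two-sided alpha 0.05 (sidedness is not stated) and power 0.90 needs 59.35, so 60 per arm and 120 in total; 120/0.90 = 133.3, so 134. This point does not touch it.

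**Scheduled observation time.** Inputs from Table 1: preoperative period 14 ± 4 days, extendable to 6 weeks (42 days); end-of-study visit at 90 ± 14 days after surgery, so 76 to 104 days. The time between admission and surgery is ignored in both arms.

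Ratio = (preoperative days + postoperative days) / postoperative days

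- 14 days: (14 + 90)/90 = 104/90 = 1.16
- 18 days: (18 + 90)/90 = 1.20
- 42 days: (42 + 90)/90 = 132/90 = 1.47
- Range over the visit windows, 10 to 18 days: from (10 + 104)/104 = 1.10 to (18 + 76)/76 = 1.24
- Range at 42 days: from (42 + 104)/104 = 1.40 to (42 + 76)/76 = 1.55

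**From time to events.** A time ratio equals an event ratio only if the daily event rate at home before surgery is the same as in the 90 days after it. Let the postoperative daily rate be k times the preoperative rate (k is an assumption; the document gives none), and suppose that controls have nothing recorded for the preoperative period. Excess in the training arm = preoperative days / (90 × k):

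| k | 14 days | 42 days |
|---|---|---|
| 1 | 14/90 = 15.6% | 42/90 = 46.7% |
| 5 | 14/450 = 3.1% | 42/450 = 9.3% |
| 10 | 14/900 = 1.6% | 42/900 = 4.7% |

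**Within the preoperative period.** Assume an equal true risk r in both arms of 2% to 20% per 14 days, with 67 patients per arm (Implementation {16c}: "The randomization is performed in a 1:1 ratio to either the intervention or the control arm"). Expected training patients with an event = 67 × [1 − (1 − r)^(days/14)].

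- 14 days: 67 × 0.02 = 1.3 to 67 × 0.20 = 13.4
- 42 days: 67 × (1 − 0.98³) = 3.9 to 67 × (1 − 0.80³) = 32.7

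The same number would occur in controls, with no scheduled visit before admission at which to look for them.

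**The case against.** Several counter-arguments stand and set the limits of the point.

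- **No comparison is planned.** The statistical methods describe no between-arm analysis of adverse events. The clinical outcomes (CCI, Clavien-Dindo grade, length of stay, readmission, mortality) concern the hospital stay or the time after surgery. A reader might infer that every safety comparison is biased. That is not supported, because from admission onward both arms share one schedule.
- **The footnote is about visits.** It says when the control group starts and does not define a reporting window. Controls must already have had Visit 1, since allocation follows consent and uses age and BMI. A reader might infer that control events are missed altogether. The text supports only that none are sought at a scheduled contact before admission. Visit 4 has both an adverse event entry and medical history, which could pick up earlier events, although no look-back is stated.
- **SAEs remain covered by a duty.** The harms section applies to both arms, and Plans for assessment and collection of outcomes {18a} names hospital records, including those from elsewhere, as source data. The schedule does not contradict that duty. It supplies an active means of meeting it before admission in one arm only. Non-serious events are the most exposed.
- **Cancelled operations are not invisible.** Every randomised patient belongs to the full analysis set, so such a control would show up as a missing outcome. The event behind the cancellation might still go unrecorded.
- **Device exposure is not confined to the preoperative weeks.** Table 1 also lists a device at Visit 6, and postoperative physiotherapy is the same in both arms.
- **The article is condensed.** The full protocol may define a collection window. The published schedule nevertheless states an asymmetry, which is more than an omitted detail.

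**Conclusion.** The point holds in a limited form. As scheduled, events between randomisation and admission are actively sought only in the training arm, so an adverse event summary by arm that includes that period would be tilted against training, and the preoperative training weeks lack like-for-like control data. Scheduled observation time is about 1.16 times that of controls with 14 days of training and 1.47 times with 42 days; the upper figure applies only to patients who train for the full six weeks.

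A reader might take these ratios to mean 16% to 47% more events in the training arm. The documents do not support that. It would require equal daily event rates before and after major abdominal surgery and no retrospective capture at Visit 4. No preoperative rate is given, and the excess shrinks as the postoperative rate rises.

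The primary endpoint, the sample size and comparisons from admission onward are unaffected. The change is worth making because it is cheap and removes an avoidable difference in ascertainment.

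**What to change.** State that AEs and SAEs are collected from randomisation in both arms. At Visit 4, ask all patients, controls included, about events since randomisation and check the available records. Where the operation is cancelled, do the same when the cancellation is recorded. In any summary by arm, tabulate randomisation to admission and admission onward separately, and note that the training arm had more intensive contact in the first period.

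The cost is a few questions and an eCRF entry at a visit that already takes place. Some recall loss for mild events in controls will remain, so the two arms will not be perfectly comparable before admission; the separate tabulation keeps this visible. Sample size and the primary analysis do not change.
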